### Questionnaires & follow-up

3.9

Participants will complete a series of validated questionnaires at baseline including the Patient Health Questionnaire – 9 Item (PHQ-9), Sheehan Disability Scale (SDS), Quick Inventory of Depressive Symptoms (QIDS), Assessment of Quality of Life (AQoL-8D), and a demographic questionnaire. The PHQ-9 and QIDS questionnaire will be used to assess depressive symptoms and the AQoL-8D questionnaire will assess the participants’ quality of life. These three questionnaires provide insight into the participant’s mental status and perceived quality of life in the context of their depression. Additionally, the SDS will be used to assess the patient’s functional impairment for the clinician group assessment during baseline. During the program, participants will complete the PHQ-9 every 3 weeks (i.e., weeks 4, 7, 10, and 13), and the QIDS and AQoL-8D at weeks 7 and 13. All questionnaires (i.e., PHQ-9, QIDS, and AQoL-8D questionnaires) will be filled at the 3, 6, and 12-month follow-up periods to measure post-study outcomes.

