### Sample size determination

3.10

In our previous clinical trials and gathered data (47), the average PHQ-9 score changed from 16.2 before e-CBT to 11.48 after 12 sessions of e-CBT (joint standard deviation; SD = 5.45). Based on these numbers, the effect size (Hedges’ G) is equal to 0.86. Given the effect size and a power of 0.8, we would need 14 participants to observe a significant effect in a paired sample *t*-test. Considering the completion rate of 45%, we would require 31 participants in each group to observe significant results. Given the two treatment arms and three treatment intensities, we would require 186 participants to detect significant clinical change across all groups. We believe this sample size is large enough to perform further analyses on factors such as the role of sex and gender in treatment efficacy and completion rate.

To follow up on this sample size determination, we will use previously collected data as mentioned above to simulate the population and use a random sampling method to determine the effect size for our power calculation. We will do this by simulating a population based on the mean and standard deviation of our previous e-CBT studies and collecting data, then randomly sampling participants to each treatment arm. This simulation will be developed using Python code. Based on this random sampling, we will calculate the effect size, set the power of 0.8, and consider the completion rate of 45% to determine the sample size required to detect a significant clinical change across the groups.

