## Statistical analysis

4

Initially, all data will be examined for missing, nonsensical, and outlying variables. Missing data will not be attributed and will be treated as missing. All statistical analyses will be performed at the end of the trial and will consider a significance level of 0.05 and 95% confidence intervals. Analyses will be conducted to account for and assess differences across sex and gender identifications, and how these factors affect the adaptability and efficacy of e-CBT.

### Hypothesis 1: outcomes in depressive symptoms of treatment arm 1 will be comparable to treatment arms 2 and 3

4.1

Clinical outcomes of the healthcare teams’ decision (arm 1) versus the AI’s decision (arm 2), will be compared by assessing the treatment completion rate, number of completed sessions, and change in questionnaire scores. The completion rate across the two study arms and three levels of care will be calculated using a 2 × 3 × 2 contingency matrix (i.e., healthcare team vs. AI × 3 different treatment intensities × completers vs. dropouts) and chi-square analysis to compare within and between completion rates in the two arms. We will use a 2 × 3 (i.e., healthcare team vs. AI × 3 different levels of care) two-way analysis of variance (ANOVA) to compare the number of completed sessions across participant groups and care levels. Questionnaires are collected at 3 different times; at the start (for all participants), midway (for those who completed at least 6 sessions), and end of the study (for those who completed the treatment program). We will use a 2 × 3 × 3 (i.e., healthcare team vs. AI × 3 different levels of care × 3 time points) linear mixed-effects model for each questionnaire to compare clinical outcomes within and between groups and times. A mixed-effects model analysis will account for any missing data caused by participant dropout. Finally, we will assess if demographic covariables affect clinical outcomes using multiple 2 × 2 × 3 × 3 (demographic factors (e.g., male vs. female) × healthcare team vs. AI × 3 different levels of care × 3-time points for the questionnaire’s score) mixed-effects model to account for each demographic variable (i.e., sex, gender, age, and income). Bonferroni corrections will follow the ANOVA analyses in *post hoc* analyses.

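### The demographic mixed models in section 4.1 are tested at 0.05, and the stated Bonferroni rule does not clearly reach them and would not control error across factors, questionnaires and interaction terms

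*Protocol article*

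**What the plan says.** Section 4 sets one rule for every analysis: they "will consider a significance level of 0.05 and 95% confidence intervals". It also gives sex and gender an analytic aim: "Analyses will be conducted to account for and assess differences across sex and gender identifications".

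Section 4.1 first specifies a 2 x 3 x 3 model (arm, care level, time), described as a "linear mixed-effects model for each questionnaire to compare clinical outcomes within and between groups and times". It then adds the demographic models: "Finally, we will assess if demographic covariables affect clinical outcomes using multiple" 2 x 2 x 3 x 3 crossings, each a "mixed-effects model to account for each demographic variable (i.e., sex, gender, age, and income").

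The next sentence holds the only multiplicity rule in the section: "Bonferroni corrections will follow the ANOVA analyses in" post hoc analyses.

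Two other places bear on the point. Section 3.9 identifies three outcome questionnaires: "All questionnaires (i.e., PHQ-9, QIDS, and AQoL-8D questionnaires) will be filled at the 3, 6, and 12-month follow-up periods". Section 3.10 says of the planned 186 participants: "We believe this sample size is large enough to perform further analyses on factors such as the role of sex and gender" in efficacy and completion.

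**The concern.** The plan states a significance level, a set of models and a correction, and the correction does not fit the models. Section 4.1 uses ANOVA for the number of completed sessions and mixed-effects models for the questionnaires, so a correction tied to ANOVA does not, on its wording, cover the demographic mixed models. A generous reading does not close the gap. Post hoc Bonferroni adjusts the pairwise contrasts that follow one effect. It leaves each omnibus term at 0.05 and does not account for four factors, three questionnaires and several interaction terms per model.

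No demographic term is singled out as the one that answers the question. Followed as written, the plan lets any term that falls below 0.05 be reported as showing that a demographic characteristic alters outcome, the effect of e-CBT or the effect of AI triage. What is at stake is the reliability of those demographic statements. The comparison of the two arms and the three hypotheses are not affected.

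**Working it through.** **The plan's own figure.** The plan gives no error rate for this family. The nearest figure is the sample size of 186 (section 3.10). It reproduces: (16.2 − 11.48)/5.45 = 0.866, stated as 0.86. A two-sided paired t-test at 0.05 with power 0.80 needs 12.7, so 13 (14 stated). Then 14/0.45 = 31.1, stated as 31, and 31 x 6 = 186. This calculation concerns change within one arm-by-intensity cell and contains no demographic test.

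**Inputs from the document.** Level 0.05 (section 4; sidedness not stated, two-sided assumed). Four factors, each in a 2 x 2 x 3 x 3 model (section 4.1). Three questionnaires (section 3.9). A separate model per questionnaire is written for the main model. For the demographic models it is the natural reading, but it is not spelled out.

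**Count.**
- Models: 4 factors x 3 questionnaires = 12.
- Terms involving the factor in each model: 1 main effect + 3 two-way + 3 three-way + 1 four-way = 8.
- Total: 12 x 8 = 96 terms.
- Expected false positives if every null is true: 12 x 0.05 = 0.6 with one test per model; 96 x 0.05 = 4.8 if every term is read. These expectations do not depend on correlation.

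**One test per model.** With independent tests, P(at least one) = 1 − 0.95^12 = 0.46. For one questionnaire alone, 1 − 0.95^4 = 0.185. The documents give no correlations, so these are assumed:

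| Assumed common correlation among the 12 tests | P(at least one false positive) |
|---|---|
| 0 | 0.46 |
| 0.3 | 0.40 |
| 0.5 | 0.32 |
| 0.8 | 0.19 |

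That is roughly 4 to 9 times 0.05. A more structured assumption (sex with gender 0.95 to 0.99, other factor pairs 0 to 0.2, questionnaires 0.5 to 0.9) gives 0.23 to 0.36, inside the same range.

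**Reading the interactions as well.** Null simulations were run with change-score linear models (factor x arm x care level), n = 186, a 33/52/15% care-level mix rounded from the earlier sample in section 3.3.2, and sex and gender assumed about 96% concordant. Results from 2,000 trials per setting:

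| Terms read at 0.05 | Scale correlation 0.5 | Range over 0.3 to 0.8 |
|---|---|---|
| Factor by arm only | 0.36 | 0.39 to 0.29 |
| Any demographic interaction | 0.73 | 0.75 to 0.63 |
| Any demographic term | 0.81 | 0.83 to 0.72 |

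A smaller run (600 trials per setting) gave 0.38, 0.77 and 0.86 at correlation 0.5, and 0.28, 0.63 and 0.72 at 0.8. These models omit time and dropout, so they indicate the order of magnitude and are not the error rate of the planned models. Treating all 96 terms as independent would give 1 − 0.95^96 = 0.993, which is too pessimistic because the tests are correlated.

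**After a correction.** Bonferroni over four named tests uses 0.05/4 = 0.0125 each. If the tests are independent, the family-wise rate is 1 − 0.9875^4 = 0.049.

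**The case against.** Several arguments on the other side have force.

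- **A correction is stated.** The Bonferroni sentence comes directly after the demographic models and closes a paragraph that covers both ANOVA and mixed models. A reader might infer that the plan has no correction at all; the text does not support that. What stands is that its scope is worded for ANOVA post hoc tests and is at best unclear for these models.
- **This is a condensed article.** A hierarchy or an exploratory label may sit in an analysis plan that is not shown, so their absence alone is not an error. The point rests on what the article fixes: a level for all analyses beside a correction that does not suit these models.
- **The analyses have lower standing.** Demographic effects are in none of the objectives or hypotheses of section 2, section 3.10 treats them as further work, and the models come last in section 4.1. This limits the consequence, but it does not exempt them from the 0.05 rule.
- **A chance finding is not shown to be likely on the base count.** With one test per model every figure is below one half. A reader might infer that a false demographic claim is more likely than not. That holds only if the interaction terms are also read at 0.05, and then only from simplified simulations whose concordance and care-level mix are assumptions. The mix comes from the algorithm's sorting of an earlier sample whose third level was video call, and it does not describe the care team's choices.
- **The earlier sample of 190 does not show that the effects are null.** Section 3.3.2 reports no significant effect of age, sex or income on sessions completed or PHQ-9 change. A reader might infer that most demographic findings in this trial would therefore be false. Gender was not tested there, everyone had e-CBT only, so arm and care-level interactions could not be examined, and non-significant p-values do not establish absence of effect.

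**Conclusion.** The point holds in limited form. Under the stated rules, the demographic mixed models are tested at 0.05 with a correction that does not clearly apply to them and would not control error across factors, questionnaires and interaction terms. The chance of at least one false positive is about 0.19 to 0.46 with one test per model, assuming 12 models, two-sided tests and correlations between 0.8 and 0. It rises to about 0.6 to 0.8 if interactions are also read at 0.05, in simulations that leave out time and dropout. The consequence is confined to what the trial may claim about sex, gender, age and income. It is worth correcting because the remedy is only wording.

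**What to change.** In section 4.1, state that the demographic models are exploratory and will be reported as estimates with 95% confidence intervals and no claim of significance.

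If the sponsor wants to keep any demographic inference, name one test per factor, on one questionnaire, that matches the question asked: for example factor by time for how e-CBT efficacy varies, or factor by arm for whether the triage method works differently across groups. Sections 3.10 and 4 ask about e-CBT efficacy, so the choice between these belongs to the sponsor and should be explicit. Apply Holm or Bonferroni over the four factors and leave all remaining demographic terms exploratory. In either case, say which analyses the existing Bonferroni sentence covers.

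The cost is a few sentences, with no change to data collection or sample size. The downside is that fewer demographic results can be called significant.

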To gather the relevant data (i.e., participant compliance and change in depression severity, as evaluated by the PHQ-9), the Triage Module was designed. As previously explained, NLP of the participants’ written accounts of their challenges with depression in the Triage Module will be used to calculate a Symptomatic Score. To verify the AI’s treatment allocation logic, completion rate and the change in PHQ-9 scores in a sample of participants (*n* = 190) who were previously enrolled in e-CBT-only treatment was assessed. The decision-making algorithm determined that the e-CBT-only program was suitable for 62 of the 190 participants (32.63%). Within these 62 participants, 53.22% (*n* = 33) had completed the e-CBT-only program in its entirety and only 20% (*n* = 12) had a final PHQ-9 score > 14. Furthermore, the algorithm indicated that e-CBT with telephone calls would be suitable for 100 out of the 190 participants (52.63%). Of the 100 participants, 41.0% (*n* = 41) completed the whole round of e-CBT-only therapy and 31.0% (*n* = 31) had a final PHQ-9 score > 14. Lastly, the algorithm indicated that e-CBT with video call was appropriate for 28 out of 190 participants (14.74%). Of these 28 participants, 35% (*n* = 10) completed the whole round of e-CBT-only therapy and 40% (*n* = 11) had a final PHQ-9 score > 14. The logic of the AI’s decision is therefore justified as those participants allocated to the e-CBT-only group had the highest percentage of completion and lowest percentage of final PHQ-9 scores >14 when completing e-CBT-only. Therefore, minimal therapist intensity is required for these individuals and e-CBT-only is sufficient. Conversely, participants allocated to the e-CBT with video call had the lowest completion rates and highest rates of final PHQ-9 scores >14 when enrolled in e-CBT-only. These findings justify the AI’s logic that greater therapist interaction is required. It is also important to note that demographic factors like age (below or above 40 years), biological sex (male or female) and income (less or more than CAD 50,000) did not have any significant effects on the number of sessions completed by participants (*p* = 0.92, 0.18, 0.90 for age, sex, and income respectively). The demographic factors did not affect the change in PHQ-9 score (i.e., the difference between the beginning and end of treatment scores) either (*p* = 0.20, 0.46, 0.39 for age, sex, and income respectively).

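### The demographic models in section 4.1 force age and income into two levels, which costs power in those supplementary analyses; a continuous or ordered term would avoid this at almost no cost

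*Protocol article*

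**What the plan says.** After the main 2 × 3 × 3 model for each questionnaire (arm, care level, time), section 4.1 adds a further set of models: "we will assess if demographic covariables affect clinical outcomes using multiple 2 × 2 × 3 × 3 (demographic factors (e.g., male vs. female"). The dimensions are spelled out in order as demographic factor, arm, care level and time point. The same sentence names the variables that go through this form: a "mixed-effects model to account for each demographic variable (i.e., sex, gender, age, and income"). Section 4.1 gives no cut-point for age or income and no reason for using two levels. Nothing in the article says that either variable will be modelled as continuous.

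Section 3.3.2 shows how the team handled the same variables in an earlier sample of 190 e-CBT-only participants: "age (below or above 40 years), biological sex (male or female) and income (less or more than CAD 50,000"). Those tests were non-significant (p = 0.20 for age and 0.39 for income on PHQ-9 change; 0.92 and 0.90 on sessions completed), and the text reads them as absence of effect.

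**The concern.** Age is continuous, and income is continuous or at least ordered before anyone groups it. A two-level factor treats everyone on one side of the cut as identical and treats people just either side of it as different. If the outcome changes steadily with age, the split discards information that was collected and weakens the test.

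The stake is the conclusion drawn from these models, namely whether demographics affect clinical outcome. Section 3.3.2 already takes non-significant tests on split variables to mean no effect. Using the same coding in a trial that expects 45% completion makes another false negative more likely. Because section 4.1 gives no cut-point, the article itself does not rule out choosing one after the data are seen.

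**Working it through.** **The plan's own figures.** The article gives no power figure for the demographic models. The only sample-size figures are in section 3.10, for a paired *t*-test within one group.
- Effect size: (16.2 − 11.48)/5.45 = 0.866; the article states 0.86.
- At 0.86, two-sided 0.05 and power 0.80, the exact paired *t* calculation gives n = 13 (power 0.812). The stated 14 gives 0.844, so the figure is reproduced to within one participant.
- 14/0.45 = 31.1, written as 31; 31 × 6 = 186. Expected completers: 186 × 0.45 = 83.7, about 84.

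These figures set the scale of the data. They were not derived for covariate effects.

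**Inputs for the check.**
- Significance level: section 4 "will consider a significance level of 0.05 and 95% confidence intervals"; two-sided is assumed.
- N = 186, or 84 completers (section 3.10).
- Age distribution: section 3.2 gives only the lower limit of 18 years, so the shape, mean and SD are assumptions and a range is shown.
- Effect of age: assumed linear.

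**Information kept by a split.** This is the squared correlation between the covariate and its two-level indicator. With q the share below the cut and c the corresponding normal quantile:
- normal covariate: φ(c)² / [q(1 − q)]
- uniform covariate: 3q(1 − q)

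| Split | Normal: kept | Uniform: kept |
|---|---|---|
| 50/50 | 0.637 (= 2/π) | 0.750 |
| 40/60 | 0.622 | 0.720 |
| 30/70 | 0.576 | 0.630 |
| 20/80 | 0.490 | 0.480 |

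More than half is lost only when one side of the cut holds fewer than about 21% of participants, under either shape.

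**If the earlier sample's cut at 40 were reused.**
- Normal age, mean 35 to 45, SD 10 to 15: 0.58 to 0.64 kept.
- Normal age, mean 30: 0.44 (SD 10), 0.51 (SD 13), 0.54 (SD 15) kept.
- Uniform age 18 to 70: q = 22/52 = 0.423, so 3 × 0.423 × 0.577 = 0.73 kept.

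**Power.** Take a linear age effect that continuous age would detect with 80% power: by the Fisher *z* approximation, a correlation of 0.204 at N = 186, or 0.302 at 84. Multiply that correlation by the square root of the information kept and recompute.

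| Split | Power, N = 186 | Power, N = 84 |
|---|---|---|
| Uniform, 50/50 | 0.676 | 0.672 |
| Normal, 50/50 | 0.604 | 0.598 |
| Normal, 30/70 | 0.561 | 0.554 |
| Normal, 20/80 | 0.495 | 0.488 |

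At N = 186, a median split of a normal covariate is worth 186 × 0.637 = 118 participants with age kept continuous.

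**Cost of the alternative.** A linear term uses one degree of freedom wherever a two-level factor uses one, both as a main effect and in each interaction, so keeping age continuous does not enlarge the model.

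**The case against.** The best reply is that the 2 is design shorthand. The only example given is male versus female, and an article may leave the exact coding of age and income to a fuller document. That holds for the missing cut-points, which alone would not be a finding. It does not hold for the structure: the sentence states a two-level factor and then lists age and income among the variables it covers.

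Second, the power figures start from an effect tuned to 80% power for a linear main effect. The planned models are repeated-measures models whose 2 × 2 × 3 between-participant layout averages 186/12 = 15.5 people per cell, or about 7 completers. Power for the interactions may well be far below 80%, and the absolute drop then shrinks: with a normal median split, 20% falls to about 14%. This stands. The share of information lost does not depend on the starting power, but the 55 to 68% is illustrative.

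Three stronger readings are tempting, and the article does not support them.
- A reader might infer that most of the information in age is discarded. That needs a cut leaving fewer than about 21% on one side, and neither a trial cut-point nor an age distribution is given.
- A reader might take 40 years and CAD 50,000 as the trial's cut-points. Section 3.3.2 uses them only for the earlier sample.
- A reader might infer that the arm comparison is left poorly adjusted. The main 2 × 3 × 3 model contains no demographic covariate, and section 3.1 plans random allocation with balancing on these same variables.

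**Conclusion.** The point holds as a limited one. Section 4.1 fixes a two-level form for age and income without giving a reason. For age, a cut near the centre of the distribution loses about 25 to 42% of the linear information and takes a test with 80% power to about 55 to 68%; the loss is larger only for a very uneven cut. This rests on a linear effect, a two-sided 0.05 test and an assumed age distribution. The loss for income cannot be sized, because section 3.9 mentions only a demographic questionnaire; if income is collected in bands, the loss would be smaller or different.

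The consequence is a higher chance of wrongly concluding that age or income has no effect, and it is confined to supplementary models. The sample size was not built on them, and where section 3.10 claims enough participants for further analyses, it names sex and gender as examples. No conclusion about the AI versus the healthcare team turns on this. It is a cheap improvement of low weight.

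**What to change.** In section 4.1, replace the single two-level form with wording by variable:
- Sex and gender stay categorical, with gender in the categories actually collected.
- Age in years enters as a centred continuous covariate.
- Income enters as a continuous or ordered score in the form collected.
- Each keeps its planned interactions with arm, care level and time. Slopes for age and income are reported with 95% confidence intervals, so that a non-significant result is not read as no effect.
- Any split at 40 years or CAD 50,000 is descriptive only.

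The cost is a sentence or two of analysis wording before the data are analysed, with no new data or participants. The downside is an assumed linear trend, which a quadratic or spline term can check.
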